**Hypothesis 2 Incidence of poor parenting**			
*Parent–child relationship*			
Strange situation procedure (SSP) – Conducted in an unfamiliar toy-filled room consisting of a structured sequence of brief episodes of separations and reunions from primary caregiver; Valid for 8–30 months^k^	X	X	
Story stem assessment – Uses dolls and narrative to measure the child’s representations of their attachment relationships; Valid for ages 3+ years^l^		X	X
Emotional availability scale (EAS) – 20 minutes free play between child and mother, coded for adult sensitivity, structuring, non-intrusiveness, non-hostility and child’s responsiveness; Valid for ages 0–7 years^m^	X	X	X
*Parenting, stress and attitudes*			
Home observation measurement of environment (HOME)–Semi-structured interview and direct observation of home environment by trained assessor to measure parent responsiveness and acceptance of the child, organisation of the environment, learning materials, parental involvement, variety of experience^n^	X	X	X
The parenting daily hassles scale – 20 items where parents rate the frequency and intensity/impact of experiences that can be a ‘hassle’ to parents^o^	X	X	X
Longitudinal Study of Australian Children (LSAC) Parenting Practices: Parent self-efficacy and harsh parenting scales	X	X	X
K6 – Measures non-specific psychological stress in adults^p^	X	X	X
Rand depression screener – 8 item self-report that screens for depressive and dysthymic disorders^q^	X	X	X
Longitudinal Study of Australian Children (LSAC) questions – Items on use of health and welfare services, employment and experience of neighbourhood	X	X	X

Notes for Table 1:

^a^Bayley N: *Bayley Scales of Infant and Toddler Development.* 3^rd^ edition. New York: The Psychological Corporation – Harcourt Brace Jovanovich; 2006.

^b^Wecshler D: *Wecshler Preschool and Primary Scale of Intelligence*. 3^rd^ edition. San Antonio TX: PsychCorp; 2004.

^c^Dunn L, Dunn D: *Peabody Picture Vocabulary Test*. San Antonio TX: PsychCorp; 2007.

^d^Waters E, Salmon L, Wake M, Wright M, Hesketh K: *Child Health Questionnaire Australian. Authorised Adaption of the Child Health Questionnaire*. Melbourne: Royal Children’s Hospital.

^e^Woodcock RW, McGrew KS, Mather N: *Woodcock-Johnston III*. Itasca IL: Riverside Publishing; 2001.

Data on background demographics and outcomes for children are being collected via standardized assessments, parent and childcare educator questionnaires, and observation and interviews. Data on parents and their outcomes – including background demographics, service usage (including childcare, counselling or social work services, usage of medical and hospital services), labour market experiences, and financial status (including income support payment history and financial stress) - is also being collected.

### Data analysis

The data analysis will identify the impact of ‘Intention to treat’ at the level of the individual child. The analysis will compare the change in an outcome measure (at time of data collection minus at baseline) for children in the intervention group with children in the control group. Impact evaluations will be conducted on outcomes measures after the 12, 24 and 36 month data collections as well following the data collection after the commencement of the first year of schooling.

For comparisons between the randomised intervention and control groups from the trial it should be possible to estimate the program impact as the difference in mean outcomes between those groups. For continuous outcome variables this will be the difference in mean changes in the outcome between intervention and control groups. For categorical outcome variables it will be differences in the change in the proportions of children in each category between intervention and control groups. For comparisons between the EYEP intervention group and the control group from LSAC a quasi-experimental matching method (difference-in-difference) will be used. Statistical significance will be established via t-tests for individual outcomes or Hotelling T tests for groups of outcomes.

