### Randomisation

After recruitment, a family is randomly assigned into either the EYEP participation group (intervention) or usual care group (control). Randomisation is done at arms-length. The random allocation into either the intervention or control group by order of recruitment into the trial is done by [name], who then provides this information to Associate [name] in sealed opaque envelopes. When a family consents to participate in the trial the SRC calls the office of Associate [name] to have the envelope opened that will reveal the status of that participant. This is done in the presence of the family whose child is being randomised.

Blocked randomisation with a variable block size is being applied to conduct the random draw using the STATA sampling without replacement procedure. In families with multiple children participating in the trial all those children will be assigned to either the treatment or control group. When a new sibling of a participant is born during the recruitment phase, the SRC will determine current eligibility of the new sibling by liaising with family services or the child protection worker. When the eligibility conditions for participation in the trial are met, then the parent is invited to consent for the new infant to participate in the EYEP trial. New siblings recruited in this way are automatically allocated to the group (treatment or control) to which their older sibling has been assigned.

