### Outcome measures

Data are being collected on participants in EYEP and the control group at the baseline (within 3 months of entry to the trial), at yearly intervals for three years after entry to the trial, and six months after commencing the first year of school (Prep grade).

Measures for data fields have been chosen on the basis of knowledge of international best-practice in measurement of child development. The measures have also been selected in order to enable comparisons with existing literature on child development and well-being and studies of previous trials such as Abecedarian, as well as to match with data items available for the alternative control group from the Longitudinal Survey of Australian Children. Table 
1 lists the categories of data being collected on children and parents that relate to the main hypotheses in this study and the instruments being used.

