### Economic evaluation

This analysis will quantify the benefits and costs of EYEP to society. Estimates of the net impacts of EYEP on children’s human capital development and service usage, and on outcomes for parents, will be translated into estimated monetary values, and these benefits aggregated to compare against the costs of the program, to arrive at a benefit-cost ratio for the program. The main potential benefits of the intervention are expected to derive from its effects on child health, cognitive development and interpersonal skills. Improved outcomes in these areas may yield benefits from: reduced direct cost to government such as reduced demands for health services, and reduced demand for specialized education due to better cognitive development. To assign monetary values to these benefits, we will for example collect information on the cost of health and special education services to estimate the values of reduced usage of those services. This information will then be combined with the estimated impacts of EYEP on service usage. The main costs associated with EYEP are the costs of providing the childcare and early education services; including employees’ wage costs, the cost of purchasing resources such as toys and educational materials, and maintenance costs for the program site. In undertaking the benefit-cost analysis of EYEP, it will be important to recognize what factors it may not be possible to value in monetary terms.

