### Sample size and power calculations

The sample size has been determined taking into account both the numbers of observations needed to have sufficient power to detect likely effect sizes and the capacity of the CPS childcare centre where EYEP is being implemented. There is no previous Australian study of an intervention similar to EYEP, therefore calculation of the required sample size has been done using impact sizes estimated for the Abecedarian project. Impact sizes from the Abecedarian project are above those for most other early years programs
[21], however, this can be attributed to its being an extensive and long-term intervention. The similar scale of intervention in EYEP makes Abecedarian an appropriate benchmark for this study. We use impact estimates from the Abecedarian project for IQ at 18 months and at 48 months (
[35] page 1918).

The sampsi routine in STATA was used to calculate the necessary sample size. When type one error is set at 0.05 and type two error set at 0.1 (power = 0.9), the minimum required sample size (per group) is 12 children based on the impact on IQ at 18 months IQ and 19 children based on the impact on IQ at 48 months. We then adjust this required sample size in two ways. First, we take into account that our sample will include families with multiple children. Based on the sample from the pilot phase of EYEP we estimate the number of children per family to be 1.35. We assume perfect correlation of outcomes between siblings which therefore requires expanding the minimum sample size by 1.35. Second, we incorporate an estimated attrition rate of 20 per cent per annum for the intervention and control groups (including item non-response). These adjustments result in a minimum sample size per group of 32 children. Hence it is expected that the sample size of 45 children in intervention and control groups will comfortably meet sample size requirements. It also provides a margin of safety in case standard errors in estimates of the impact of EYEP are larger than for the Abecedarian trial. All children in the Abecedarian trial were enrolled prior to reaching 6 months of age, while children recruited into the EYEP trial have been from a broader range of ages, up to 3 years. To the extent that age of enrolment is a source of variability in impact sizes, our estimates of impact size may therefore have larger standard errors than the Abecedarian study.

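### The only stated unit of analysis is the child, so parent-level measures repeat across siblings and a later-born sibling's parent baseline can fall after EYEP exposure

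*Protocol article*

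**What the plan says.** The Aims and hypotheses section includes a hypothesis about parents: less poor parenting and more engagement with services. Table 1 of the Protocol article lists measures for it that describe the adult rather than a particular child: the K6, the depression screener, parenting daily hassles, parent self-efficacy, and the LSAC items on service use and employment. These are taken at entry, annually and at school.

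The Data analysis section sets one unit, "The data analysis will identify the impact of ‘Intention to treat’ at the level of the individual child", and one derivation: "The analysis will compare the change in an outcome measure (at time of data collection minus at baseline) for children in the intervention group". Testing is equally general: "Statistical significance will be established via t-tests for individual outcomes or Hotelling T tests for groups of outcomes". No parent or family unit is given, and the tests are not adjusted for families.

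On siblings, the Randomisation section states: "In families with multiple children participating in the trial all those children will be assigned to either the treatment or control group". It adds, for children born during recruitment: "New siblings recruited in this way are automatically allocated to the group (treatment or control) to which their older sibling has been assigned". The Outcome measures section schedules data collection "at the baseline (within 3 months of entry to the trial), at yearly intervals for three years after entry to the trial".

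For the sample size, "we estimate the number of children per family to be 1.35". The Economic evaluation section says that estimated impacts, including those "on outcomes for parents, will be translated into estimated monetary values, and these benefits aggregated to compare against the costs of the program".

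**The concern.** A rule written for children is the only rule available for parents, and it fits them badly in two ways.

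First, a parent with two trial children contributes two records. If the children enter together, a K6 change is the same number entered twice. The mean then weights parents by their number of trial children, and the t-test treats the copies as independent.

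Second, a sibling born and enrolled later has an entry assessment of its own. By then the family has been randomised. In the EYEP arm the parent may already have been engaged by the program, including the care team meetings held every 12 weeks that the Background describes. Recruitment ran from 2011 to an expected end in early 2015, so that exposure could exceed a year. Subtracting such a baseline can remove part of the effect being estimated.

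At stake are the parent-hypothesis tests, possibly the size of the parent estimate, and possibly the parent component of the benefit-cost ratio.

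**Working it through.** **Inputs.** 45 children per arm (Abstract; Sample size section); 1.35 children per family, a pilot estimate, and perfect sibling correlation (Sample size section). The later-born share of siblings and the time course of any parent effect are not given.

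**The plan's own figure.** The stated minimum of 32 per group reproduces: 19 × 1.35 / 0.8 = 32.06 (12 × 1.35 / 0.8³ = 31.6 also rounds to 32). It is not disputed here. It shows that the sample size allows for siblings, while the stated tests do not.

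**1. Repeated parents.**
- Families per arm: 45 / 1.35 = 33.3.
- Extra records: 45 − 33.3 = 11.7 per arm, and 11.7 / 45 = 26%.

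**2. Type I error when a parent's values are identical across siblings** (normal approximation).
- If families have one or two children, 65% have one and 35% have two. The design effect is Σm²/Σm = (0.65 × 1 + 0.35 × 4) / 1.35 = 2.05 / 1.35 = 1.52.
- Effective n is 45 / 1.52 = 29.6 per arm.
- True two-sided alpha is 2 × [1 − Φ(1.96 / √1.52)] = 0.11.
- With the plan's own inflation factor of 1.35 as the design effect, alpha is 2 × [1 − Φ(1.96 / √1.35)] = 0.09.

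**3. Later-born siblings.** Let s be the share of extra children who are later-born, and g the fraction of the parent effect already present when they enter.
- Plateaued effect: the later record shows only (1 − g) of the effect, so the mean change in the EYEP arm is attenuated by s × 0.259 × g.
  - s = 0.25, g = 0.25: 1.6%
  - s = 0.5, g = 0.5: 6.5%
  - s = 1, g = 1: 25.9%
- Steady accrual at r per year, sibling entering at year 2: the first child's 36-month record shows 3r, and the sibling's shows 5r − 2r = 3r. Attenuation is zero.

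The values of s and g are assumptions.

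**4. Benefit aggregation.**
- Parent impact multiplied by children: 45 / 33.3 − 1 = 35% too many parents.
- Parent impact multiplied by families: 0%.
- The Economic evaluation section names neither multiplier.

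**The case against.** The strongest reply is that no sentence says a parent measure is stored once per child or scored against each child's own entry. The analysis text is worded for children, parent data are described separately under Outcome measures, and a condensed article may leave record structure to a fuller document. Sibling dependence is also recognised in the sample size, and weighting parents by number of trial children is a possible estimand.

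Part of this stands. The per-child structure is a literal reading of a general rule, not an explicit derivation for parents. But the article does more than stay silent: it fixes the child as the unit, with no exception, although one of its hypotheses concerns adults. Enlarging the sample protects power; it does not correct a t-test that treats siblings as independent. A child-weighted estimand does not justify a post-exposure baseline either.

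Three stronger readings do not hold:
- A reader might infer that the benefit-cost ratio counts some parents twice. A child-level mean difference re-weights families but does not double a benefit; an overcount needs multiplication by children, which is not stated. The same section expects the main benefits to come through the children, and the effect on the ratio cannot be worked out from the article.
- A reader might infer that the parent effect is necessarily pulled toward zero. That requires the effect to flatten; under steady accrual nothing is lost. Control families' later baselines are also post-randomisation, and the article accepts that trial participation may change their choices.
- A reader might infer that everything listed under the parenting hypothesis should become one record per family. The Emotional Availability Scale, Strange Situation, story stem and child-specific HOME items describe a particular child or pair, so a record per child is proper.

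**Conclusion.** The point holds for purely parent-level measures. As written, the analysis rule repeats a parent for about 26% of records per arm. An unclustered 0.05 t-test then has a true alpha of about 0.09 to 0.11, assuming identical repeated values and 1.35 children per family. A later-born EYEP sibling's parent baseline falls after randomisation and exposure. Attenuation from this lies between zero (steady accrual) and about 26% (plateau reached and every extra child later-born), and the article does not allow it to be placed within that range. Siblings who enter together do not have the baseline problem. Overcounting of parent benefits is an open question, 0% or 35% depending on the multiplier, and not a demonstrated error.

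**What to change.** In the Data analysis section:
- Analyse purely parent-level measures (K6, depression screener, parenting daily hassles, parent self-efficacy, LSAC service-use and employment items) with one record per randomised family. Take baseline at the first enrolled child's entry and time the waves from that entry. Do not use a later sibling's entry assessment as a parent baseline.
- State which child's Prep-grade assessment supplies the parent's school-time value; the first enrolled child's would be consistent.
- Keep child-specific and dyadic measures per child, with family-clustered standard errors. Assign the harsh-parenting scale to one group or the other according to whether its items refer to a particular child.

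In the Economic evaluation section, state that parent impacts are multiplied by the number of families and child impacts by the number of children.

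The cost is wording. The first child's entry and annual parent data are already scheduled. Parent records fall from 45 to about 33 per arm, but most of those dropped are repeats. Where a parent's values are identical across siblings, precision does not suffer: 33.3 independent families compare with an effective 29.6 under child weighting. Some later readings of the same parent, taken on a sibling's schedule, would go unused.

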**Methods/Design:**

The RCT is being conducted with 90 participants (45 intervention and 45 control). Eligible children must be aged under three years and assessed as having two or more risk factors as defined in the Department of Human Services *Best Interest Case Practice Model*. The intervention group participate for three years (or until school entry) in EYEP. The trial does not provide any early years education or care to the control group. Data are being collected on outcome measures for participants in EYEP and the control group at the baseline, at yearly intervals for three years, and six months after commencing the first year of school. Outcome measures encompass children’s health and development, academic ability and emotional and behavioural regulation; and quality of parenting practices. The study will evaluate the impact of EYEP on these outcomes, and undertake a benefit-cost analysis of the program.

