The **education** model in EYEP is a pedagogically-driven reflective teaching model that is child-focused and built on the *National Early Years Learning Framework* of ‘Belonging, Being and Becoming’
[31]. Each child has individual learning goals developed by the educators in partnership with families. Educators plan a curriculum using play-based approaches and intentional teaching to support each child’s learning and development across learning outcomes in the *Early Years Learning Framework*. Play-based approaches and intentional teaching support children to develop a positive sense of identity as they explore, create, imagine, solve problems, learn communication skills, and develop friendships. It is understood that how children learn is just as important as what they learn. Reflection on practice guides the on-going planning cycle. Educators document, monitor and assess each child’s learning over time.

The EYEP model actively engages with **parents** to encourage on-going participation in the program, as well as in enhancing their usage of all available health, educational and social services available, in order to improve outcomes for children. At-risk children and their families characteristically have concurrent barriers which affect their inclusion in early childhood services; for example, chaotic lifestyles; mental health and substance abuse issues; family violence; low levels of educational attainment; insecure housing arrangements; and antisocial behaviour. Consequently, EYEP aims to sustain parental involvement and minimize attrition levels by improving parental engagement in their children’s development. In order to achieve this, care team meetings incorporating parents and family support/child protection workers and the early years educators (primary worker for the child) will take place every 12 weeks. These meetings aim to identify, with parents, the goals and aims they would like to achieve for their children, which is then documented on agreement forms and reviewed every 12 weeks.

EYEP can be seen as addressing a variety of barriers that might otherwise exist to families taking advantage of supportive services – such as affordability; families beliefs that may place low priority on early education services; and inter-personal barriers including beliefs and attitudes on the part of service providers that might compromise engagement
[32].

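### Separate t-tests on change at each wave can use only children with both scores; on the plan's own attrition rate, about 49% would lack a usable value at 36 months

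*Protocol article*

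**What the plan says.** Under Data analysis, the protocol article sets the principle: "The data analysis will identify the impact of ‘Intention to treat’ at the level of the individual child". The analysis variable follows: "The analysis will compare the change in an outcome measure (at time of data collection minus at baseline". The times are given next: "Impact evaluations will be conducted on outcomes measures after the 12, 24 and 36 month data collections", with a further evaluation after school entry. For continuous outcomes the estimator is the between-arm contrast of mean change. The test is also named: "Statistical significance will be established via t-tests for individual outcomes or Hotelling T tests for groups of outcomes". The section does not define an analysis set and does not say how a child without a score at a wave is handled.

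Under Sample size and power calculations, the article allows for "an estimated attrition rate of 20 per cent per annum for the intervention and control groups (including item non-response". That rate is used only to enlarge the sample.

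Under Approaches to dealing with the problem, the programme is described as working to hold families in: "EYEP aims to sustain parental involvement and minimize attrition levels by improving parental engagement".

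**The concern.** A t-test on change needs a baseline score and a score at the wave in question. Hotelling T is stricter, because it needs every outcome in the group. Taken as written, each evaluation is therefore an available-case analysis, and the plan itself expects the available cases to shrink a good deal by 36 months.

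Two things are at stake. The first is information: a child assessed at entry, 12 and 24 months but not at 36 months contributes nothing to the 36-month contrast. The second is validity: grouping children by assigned arm does not recover the effect in all randomised children if those without a score differ from those with one, and differ in a way that is not the same in the two arms. The article describes families with unstable housing, substance abuse and violence at home, which could plausibly affect both follow-up and child outcomes. It also describes a programme that meets families every 12 weeks, whereas controls receive usual care and, like all children, the trial's assessments and an annual development report. The sample size section nevertheless applies one rate of loss to both arms.

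**Working it through.** **Inputs**

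- Children per arm: 45 (Abstract, Methods/Design: "The RCT is being conducted with 90 participants (45 intervention and 45 control").
- Loss: 20% a year in each arm, item non-response included (Sample size and power calculations).
- Base requirement per group: 12 (IQ at 18 months) or 19 (IQ at 48 months); sibling factor 1.35; stated minimum 32; type I error 0.05; power 0.9 (same section).
- Instruments by time point: Table 1.

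**1. The plan's own figure.** Required n = base × 1.35 / retained share. The stated 32 can be reached in two ways:

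- 19 × 1.35 / 0.80 = 32.06 (one year of loss).
- 12 × 1.35 / 0.80³ = 16.2 / 0.512 = 31.6 (three years of loss, smaller base).

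Which route was used is a separate question. Either way, a child without a value is treated as contributing nothing. That fits an available-case analysis but does not prove one.

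**2. Usable values at each wave, if the yearly rate compounds.** Retained = 45 × 0.8^years.

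| Wave | Retained share | Per arm | Without a usable value |
|---|---|---|---|
| 12 months | 0.800 | 36.0 | 20% |
| 24 months | 0.640 | 28.8 | 36% |
| 36 months | 0.512 | 23.0 | 48.8% |

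If the rate instead means 20 points of the starting sample each year, 60% are without a value at 36 months and 45 × 0.40 = 18 per arm remain.

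**3. Information set aside at 36 months.** About 45 − 23.0 = 22 children per arm lack the 36-month value. If all loss were permanent drop-out, 36.0 − 23.0 = 13 of them would have at least a 12-month score, and 45 − 36 = 9 would have an entry score only. Because the rate includes item non-response, which can come and go, this split is approximate.

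**4. Power.** The article gives no standardised effect. Solving back from 19 per group, two-sided (an assumption): d = (1.960 + 1.282) × √(2/19) = 1.05. With siblings perfectly correlated, as the article assumes, the effective n at 36 months is 23.04 / 1.35 = 17.07 per arm. Power = Φ(1.05 × √(17.07/2) − 1.960) = Φ(1.11) = 0.87, against the 0.90 intended. For so large an effect the loss of power is small, so the case for change rests on the unused data and the exposure to bias.

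**5. When bias arises.** Let p be the share without a score in an arm, and g the mean change in children with a score minus that in children without. The available-case contrast is off by p × g in the intervention arm minus p × g in the control arm. It is zero if the products match. Because the variable is change, a stable difference in level between the two kinds of child cancels; only a difference in change matters. The article gives neither p by arm nor g, so no size follows.

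**6. What a model can use.** In Table 1 the Bayley scales, DECA, HOME, the Emotional Availability Scale, and the parenting and stress scales are taken at entry and again later. WPPSI, Peabody, Expressive Vocabulary and the Child Behaviour Checklist have annual and school scores but no entry score, so change from entry on the same instrument does not exist for them. Woodcock-Johnson is taken at school only.

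**The case against.** The strongest objection is that this is a condensed article and that handling of missing outcomes normally sits in the full protocol or analysis plan, which is not shown. A contrast of mean change with a t-test could be run after multiple imputation or with weights. As an answer to a complaint about silence, that stands. It does not fully answer the present point, because the article names an estimator and a test, and a likelihood model using all waves would have to replace them.

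A reader might infer that the article contradicts its own intention-to-treat label. It does not: analysing children in their assigned arm, whatever their attendance, satisfies the label, and a child who leaves the programme can still be assessed.

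A reader might also infer that 49% of randomised children are excluded from the trial's analysis. The article never says that anyone is excluded. The rate includes item non-response, so 49% is an expected share without a usable value for an outcome, not a count of children unseen.

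The passage on minimising attrition concerns families staying in the programme. That retention in assessments will differ by arm is an inference from it, not a stated fact.

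It is also fair to say that a model restricted to children with some follow-up would still drop those lost before 12 months, about 9 per arm under permanent drop-out, and that any such model leans on missing at random. The fix below addresses the first; only sensitivity analysis can address the second.

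**Conclusion.** The concern holds as a choice of method that can be improved, not as a contradiction. Analysed as written, the 36-month contrast would rest on about 23 of 45 children per arm, with 48.8% lacking a usable value for an outcome. This assumes that the 20% rate compounds, applies equally to both arms and is borne out; the linear reading gives 60% and 18 per arm. Earlier scores on the missing children would play no part in that contrast. Bias is possible if loss differs by arm or relates to family functioning. The document makes this plausible but does not show it, and gives no basis for a direction or size. The change is worth making because the extra data are already being collected.

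**What to change.** - **Instruments measured at more than one wave:** replace the separate t-tests by one likelihood-based repeated-measures model with arm-by-wave effects, and read the contrast at each wave from it.
- **Where an entry score on the same instrument exists:** treat it as part of the outcome vector, so that all randomised children with an entry score stay in the model even without follow-up.
- **Where none exists** (WPPSI, Peabody, Expressive Vocabulary, Child Behaviour Checklist): adjust for a related entry measure, such as the Bayley scales for the cognitive tests, and for age.
- **School-only measures** (Woodcock-Johnson): use regression adjusted for a related entry measure and age, with family-clustered standard errors.
- **Siblings:** use family-clustered standard errors or a family random effect throughout, because siblings are allocated together. With about 1.35 children per family a random effect may be weakly estimated, which favours the clustered errors.
- **Missing outcomes:** state the analysis set, report missing outcomes by arm and wave, and add a delta-adjusted sensitivity analysis that lets the assumed shortfall in unobserved children differ by arm.

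The cost is a change of analysis wording and modest programming, with no new data. The main analysis would rely on missing at random, which the sensitivity analysis is there to test.
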